## Abstract

**Background:**

Congenital hemiplegia is the most common form of cerebral palsy (CP) accounting for 1 in 1300 live births. These children have limitations in capacity to use the impaired upper limb and bimanual coordination deficits which impact on daily activities and participation in home, school and community life. There are currently two diverse intensive therapy approaches. Traditional therapy has adopted a bimanual approach (BIM training) and recently, constraint induced movement therapy (CIMT) has emerged as a promising unimanual approach. Uncertainty remains about the efficacy of these interventions and characteristics of best responders. This study aims to compare the efficacy of CIMT to BIM training to improve outcomes across the ICF for school children with congenital hemiplegia.

**Methods/Design:**

A matched pairs randomised comparison design will be used with children matched by age, gender, side of hemiplegia and level of upper limb function. Based on power calculations a sample size of 52 children (26 matched pairs) will be recruited. Children will be randomised within pairs to receive either CIMT or BIM training. Both interventions will use an intensive activity based day camp model, with groups receiving the same dosage of intervention delivered in the same environment (total 60 hours over 10 days). A novel circus theme will be used to enhance motivation. Groups will be compared at baseline, then at 3, 26 and 52 weeks following intervention. Severity of congenital hemiplegia will be classified according to brain structure (MRI and white matter fibre tracking), cortical excitability using Transcranial Magnetic Stimulation (TMS), functional use of the hand in everyday tasks (Manual Ability Classification System) and Gross Motor Function Classification System (GMFCS). Outcomes will address neurovascular changes (functional MRI, functional connectivity), and brain (re)organisation (TMS), body structure and function (range of motion, spasticity, strength and sensation), activity limitations (upper limb unimanual capacity and bimanual motor coordination), participation restrictions (in home, school and recreation), environmental (barriers and facilitators to participation) and quality of life.

**Discussion:**

This paper outlines the theoretical basis, study hypotheses and outcome measures for a matched pairs randomised trial comparing CIMT and BIM training to improve outcomes across the ICF.

**Trial Registration:**

ACTRN12609000912280

## Background

Cerebral palsy (CP) is the leading cause of childhood disability with an incidence of 1 in 500 live births[1]. Hemiplegia accounts for 35% (1 in 1300) of these children and upper limb (UL) involvement is usually more pronounced than the lower limb[2]. Management of long-term disability and the burden of care on both the health care system and families are substantial. Recently the financial cost of CP was estimated at Aus$1.47 billion with Aus$124.1 million attributed to direct program costs[3]. Families and individuals with CP accommodate approximately 43% of these costs and the various levels of government the remainder[3].

From an individual perspective, the impact of hemiplegia can be described using the International Classification of Functioning, Disability and Health (ICF)[4]. At the level of Body Structure and Function, children with hemiplegia can present with changes in brain structure and function (structural MRI, neurovascular changes with fMRI) resulting in impairments of spasticity, muscle length, sensation, and weakness. Limitations in activity performance are common in areas such as self-care, school and household related activities. Participation can be restricted in home, school and broader community life and may in turn impact on quality of life (QOL). Intervention is therefore paramount to minimise long term disability, and optimise functional independence, societal participation and long term career aspirations.

There are many models of intervention targeting deficits in hand and arm function that aim to reduce activity limitations for children with congenital hemiplegia. Historically, neurodevelopmental treatment approaches (NDT) have been used in an attempt to ameliorate impairments of body structure and function with the assumption that this would transfer to gains in activity performance[5]. However there has been little empirical evidence to support these approaches[6,7]. Current management of motor dysfunction includes task-oriented, functional therapy or motor learning approaches that collectively use repetitive practice of functional and goal directed tasks[8-10]. The framework of dynamic systems theory underpins some of these contemporary approaches[11,12]. This theory purports that spontaneous movement is generated as a product of the interaction of many systems. These systems include the child, the task and the environment and the movement is generated in the most efficient manner for a particular moment[12].

Constraint induced movement therapy (CIMT) is a relatively new intervention derived from the basic sciences[13]. It comprises applying a restraint to the unimpaired UL coupled with intensive training of unimanual skills in the impaired hemiplegic limb. This approach has been shown to improve UL task performance in adults following stroke with retention of effects at twelve months post intervention[14]. Modification of this approach for children with CP has followed, but until recently efficacy was limited to case reports and small prospective studies[10,15-20]. Two small RCTs have been performed with positive effects for amount of use and emerging behaviours[10,21]. A Cochrane review concluded that there was emerging evidence supporting CIMT for children with hemiplegia[22]. A further systematic review[7] that investigated all UL interventions including CIMT, NDT and contemporary upper limb therapy included three RCTs of CIMT[10,21,23]. Pooling of CIMT data for meta-analysis was not possible due to small sample sizes, variation in the type of restraint used, differing outcome measures (many of which had no reported validity or reliability for the population), varying intensity, and dosage of intervention made comparison across trials difficult[7]. Our systematic review concluded that evidence for CIMT should therefore be viewed cautiously and recommended that further suitably powered RCTs using valid and reliable outcome measures were required.

Conceptually, there are a number of key difficulties in the application of CIMT to children with CP. Children with hemiplegia, unlike adults who acquire a hemiplegia subsequent to a stroke, have never learned to use their UL effectively so demonstrate developmental disregard and/or non-learned use of their impaired limb[10,16]. Consideration of developmental aspects of acquiring UL skills and critical periods of brain development related to UL co-ordination are therefore important. Early bimanual use of both hands is thought to be important for the development of the assisting hand, as the development of motor control is modelled on effective use of the dominant hand[24]. In healthy adults, the contralateral and ipsilateral sensory motor cortex appear to act in a co-ordinated fashion during unilateral hand movements[25]. Constraint or reduced use of the dominant hand in young children may lead to activity dependent competitive displacement of the surviving contralateral corticospinal projections from the affected cortex by more active ipsilateral corticospinal projections from the affected motor cortex, thereby compounding the problem[26]. In addition, children with hemiplegia have bimanual coordination difficulties over and above their unimanual deficits[27]. The relationship between unimanual capacity and bimanual performance is not clearly understood and it is uncertain whether gains in unimanual capacity will transfer into improvements with bimanual performance. A discrepancy between unimanual capacity and bimanual performance is often observed in these children. When doing functional tasks such as putting on shoes and socks, children may adeptly use their unimpaired limb with little involvement of their impaired limb. However, when directed to do tasks with their hemiplegic limb they can demonstrate unimanual skills that are not utilised in bimanual tasks. Motor learning principles would suggest that improvement in use of two hands together will be maximised by repetitive practice of bimanual goal directed tasks[27].

Historically, therapists have focused on a bimanual approach (BIM training) in the management of motor dysfunction in children with hemiplegia[28]. Recently, a publication of intensive bimanual training, Hand Arm Bimanual Intensive Training (HABIT) was described by Charles and Gordon[27]. This approach focused on equal use of both hands in bimanual tasks and was developed in response to the limitations of CIMT to address bimanual co-ordination while maintaining the positive aspects of intensive training of the impaired limb[27]. A small RCT compared HABIT (n = 10) to a delayed treatment group (n = 10). Treatment intensity was equivalent to that employed in CIMT trials, for 6 hours per day over a 10-day period (total 60 hours training). A small treatment effect (η^2 ^of 0.256) favouring HABIT was achieved on a validated bimanual assessment the Assisting Hand Assessment (AHA)[29]. To date, CIMT and BIM training have not been directly compared in a randomised clinical trial. A further limitation of all previous studies of UL interventions has been the lack of standardisation of intensity or environmental context for the comparison or control treatments[7]. These parameters will be addressed in the present study.

The current study is funded by the National Health and Medical Research Council (NHMRC) of Australia (project grant 368500). The broad aim of this study is to evaluate in a single blind randomised matched pairs comparison trial whether a novel rehabilitation, CIMT, is more effective than BIM training to improve UL function, societal participation and QOL in children with congenital hemiplegia aged 5 to 16 years.

## Methods/Design

A matched pairs randomised trial will be conducted using an activity based day camp model[30] to evaluate the efficacy of CIMT compared to BIM training in children with congenital hemiplegia aged 5 to 16 years.

The specific hypotheses to be tested are:-

1. CIMT will reduce activity limitations and participation restrictions to a greater extent than BIM training in children with hemiplegia.

2. CIMT will result in greater use-dependent brain reorganisation compared to BIM training and this cortical plasticity will be retained for longer periods.

3. CIMT will result in greater enhancement of participation in school and community roles.

4. CIMT will result in greater improvements in QOL.

These hypotheses will address the following specific aims:-

1. Upper limb rehabilitation consumes a great deal of time and is costly, and the effects may be short lived. CIMT is a novel upper limb training where the unimpaired arm is constrained in a "glove like splint" while the impaired hemiplegic arm is intensively trained. This study will determine which training approach has the greatest impact on activity limitations and how long that effect is retained.

2. If one approach results in greater enhancement and retention of cortical reorganisation then this will guide clinical practice with implications for other patients (Traumatic Brain Injury TBI, stroke). An understanding of the nature and timing of the brain lesion may indicate which children respond better.

3. If a training program enhances community participation and improves QOL this will have a profound impact on educational opportunities and vocational roles.

Assessments will be performed at baseline prior to the camp and then at three weeks following completion of the camp. Further follow-up will be performed at 26 and 52 weeks following intervention to determine retention of effects. The experimental design and outcome measures are depicted in Figure 1.

**Figure 1 F1:**
[figure not shown]
**Flow chart of INCITE study according to CONSORT guidelines**.

The research ethics boards at the Royal Children's Hospital, Melbourne (HREC 26074 A,B,C,D), La Trobe University (HEC 06-68), Royal Children's Hospital, Brisbane (HREC 2008/018) and The University of Queensland (2008000961) have granted approval for the study.

### Study sample and recruitment

Children and youth will be recruited from across Victoria and Queensland, Australia. The Australian health system allows all individuals access to publicly funded services and reimbursement for private medical specialists. The recruitment process will target both publicly funded services and private practitioners with the expectation that the sample will be representative of children with congenital hemiplegia. Furthermore, financial support for families from regional areas will be made available to allow equity of access to the program and a representative sample of children from metropolitan, outer metropolitan and rural/regional/remote areas.

### Inclusion criteria

The study will include children and youth:

1. With a confirmed diagnosis of congenital hemiplegia.

2. Aged 5 to 16 years.

3. With predominant spasticity rather than dystonia interfering with UL function according to the classification of motor type by Sanger et al[31] with Modified Ashworth Scale (MAS) grade >1 but <3[32].

4. Ability to achieve minimal active grasp with the impaired hand.

5. Sufficient co-operation and cognitive understanding to participate in the group activities.

For a subset of children performing the Advanced Brain Imaging and Transcranial Magnetic Stimulation (TMS) studies further inclusion criteria are:-

1. Sufficient co-operation to perform Advanced Brain Imaging studies for 45 minutes.

2. No exclusions for 3 tesla Magnetic Resonance Imaging (3T MRI) including no metal implants, no shunts, no uncontrolled epilepsy as the later would be a confound.

3. For TMS there must be no current or previous history of epilepsy.

### Exclusion criteria

1. Severe muscle spasticity and/or contracture (MAS > grade 3, i.e. muscle contracture or rigidity) which would require spasticity management or serial casting.

2. Previous orthopaedic surgery in the UL.

3. Serial casting or Botulinum Toxin A (BoNT-A) injections in the UL within 6 months prior to study entry.

### Sample size

According to CONSORT guidelines the primary basis for sample size calculation is adequate power for the comparison between the functional effects of CIMT and BIM training at 3 weeks post intervention. Based on data from a previous study[33], a mean difference of 7 percentage points was proposed or 10% of the anticipated control group mean at baseline on the Melbourne Assessment of Unilateral Upper Limb Function[34] as the minimum difference that is likely to have substantial clinical importance. Our pilot data in a study of UL training with and without intramuscular BoNT-A injections yielded standard deviation of changes of 7.6 and 9.6 units in the two groups. Based on a t-test comparison of changes using a SD of 9 units for both groups, significance (alpha) level of 0.05, and 80% power, we require 26 participants in each group (total sample of 52).

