### Randomisation

Children will be matched in pairs according to age (12 month age bands), gender, side of hemiplegia, and level of functional ability based on MUUL scores at screening. Once matching has been achieved and baseline assessments completed, children will be randomised within pairs from concealed envelopes opened by non-study personnel. Treatment allocation will be recorded on a piece of folded paper inside each envelope in random order (computer generated). The randomisation process will involve allocating a number "1" or "2' to each member of the pair which will be written on the paper inside the envelope. As each pair is entered, they will be allocated the next consecutive envelope, which will be opened by the non-study personnel who will read and record the treatment allocation from the paper inside the envelope. Study personnel will be informed of group allocation.

A matched pairs design is the design of choice as it minimises the likelihood of group differences at baseline that has often been present in UL rehabilitation studies[21,29]. In order to maximise group coherence, camps will be conducted in two age bands (two camps each of CIMT and BIM training for children 5-10 years and one camp each of CIMT and BIM training for children 11-16 years).

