### Study treatments

Each intervention will be delivered in groups of 9 to 13 children for 6 hours per day for 2 weeks (10 days) in a day camp model. The total dosage of intervention will be 60 hours. After baseline assessment and randomisation children will attend either the two week BIM training camp or immediately following, a two week CIMT camp. One week of the camp will be during school term and one during school holidays. To optimize children's engagement in the intervention, day camps will be run at a community sporting facility and will employ a circus theme with circus activities provided by professional trainers and an additional day-excursion to an adventure "low ropes" course. Consistent with self determination theory[35] to maximize motivation the key elements of competence, autonomy and relatedness will be incorporated. Competence will be achieved through scaffolding of activities to optimise success, autonomy by allowing choice, and relatedness through the sharing of the experience with others of similar abilities.

Both groups will receive the same dosage and content of intervention, delivered in the same environment. Participants in the CIMT group will wear a tailor made glove on their unimpaired limb while attending the day camp, which will only be removed for toileting. Table 1 summarises the components of each intervention. The tasks for each camp will be designed to enable either maximal bimanual use of the hands for the designated tasks and modified for the CIMT camp to perform the same tasks in a unimanual approach with constraint on the unimpaired hand.

**Table 1 T1:** Summary of intervention content

Session (and Activities)	Allocated Time	CIMT: Type of involved hand use	BIM training: Type of involved hand use

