#### 2. Primary and Secondary Outcome Measures

The primary outcome measure of interest is UL activity performance for unimanual capacity using the Melbourne Unilateral Upper Limb Assessment at 26 weeks follow up. Secondary measures include measures across all domains of the International Classification of Functioning, Disability and Health (ICF).

Measures of body structure will include both the positive features of the upper motor neurone syndrome (muscle spasticity, length) and the negative features (weakness, dexterity and sensation). Positive features will be assessed in the impaired (hemiplegic UL) while negative features will be compared between limbs (to account for any unintended effects of wearing the constraint on the unimpaired hand in the CIMT group).

Measures of activity will assess unimanual capacity in the impaired limb (using the MUUL), bimanual performance between the upper limbs (using the Assisting Hand Assessment) and the achievement of individualised outcomes (with the Canadian Occupational Performance Measure). Participation will be assessed at home, in school and community life using both child and parent proxy response. Environmental barriers and facilitators to participation will be evaluated. In addition to these measures, the broad domains of quality of life will be assessed.

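### The 52 children required for 80% power are also the 52 to be recruited, so there is no allowance for loss, and the power is stated for 3 weeks while the primary outcome is at 26 weeks

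*Protocol article*

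**What the plan says.** The Sample size section of the protocol article bases the calculation on the comparison of the two therapies 3 weeks after the intervention. Its inputs are:

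- Difference to detect, on the Melbourne Assessment: "a mean difference of 7 percentage points was proposed or 10% of the anticipated control group mean at baseline".
- Pilot data, which "yielded standard deviation of changes of 7.6 and 9.6 units in the two groups".
- Test, SD, alpha and power: "Based on a t-test comparison of changes using a SD of 9 units for both groups, significance (alpha) level of 0.05, and 80% power".

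The result is that "we require 26 participants in each group (total sample of 52").

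The Abstract (Methods/Design) carries the same number over as the recruitment target: "Based on power calculations a sample size of 52 children (26 matched pairs) will be recruited". The section on primary and secondary outcome measures defines the primary outcome "using the Melbourne Unilateral Upper Limb Assessment at 26 weeks follow up". The Analyses section plans intention-to-treat analyses, with independent t-tests or rank sum tests between groups at each of the three follow-ups.

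**The concern.** A number required for a stated power is a number with outcome data. A number recruited is normally larger, to cover children who are not assessed. Here the two are the same, so the plan's own figures set the allowance for loss at zero. This does not depend on a document we cannot see: both numbers are stated, and one is said to follow from the power calculation.

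The time point adds to the problem. The 80% is given for 3 weeks, but the primary outcome is at 26 weeks, so the article gives no power for its primary comparison. Full retention is also harder to assume at half a year than at three weeks, with families drawn from two states including remote areas.

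At stake is how a non-significant primary result would be read. Set against a claimed 80%, it would seem to speak more strongly against a 7-point difference than the trial can support.

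**Working it through.** **Inputs.** From the Sample size section: difference 7, SD of change 9 in both groups, alpha 0.05, power 80%, t-test on changes. Sidedness is not stated. A one-sided calculation would need only 21 per group, so the plan's figure is two-sided. Allocation is 1:1, because "children will be randomised within pairs from concealed envelopes opened by non-study personnel".

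**Step 1. Reproduce the plan's figure (normal formula).**

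n per group = 2 × (SD/difference)² × (z₀.₉₇₅ + z₀.₈₀)² = 2 × (9/7)² × (1.960 + 0.842)² = 25.95, rounded up to 26.

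The plan's figure is reproduced. By the same approximation, power at 26 per group is 80.1%, and at 25 it is 78.5%. Losing one child per group takes power below 80%.

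**Step 2. Power of the planned test (noncentral t).**

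Noncentrality = 7 / (9 × √(2/n)), with 2n − 2 degrees of freedom. At n = 26 this is 7 / (9 × √(2/26)) = 2.80, with 50 degrees of freedom and critical value 2.009. Power is 78.5%. At n = 27 it is 80.1%.

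**Step 3. Power after loss.** The document gives no loss rate, so 5% to 20% is an assumed range. The difference and SD are assumed to be the same at 26 weeks as at 3 weeks. The number analysed per group is 26 × (1 − loss).

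| Assumed loss | Analysed per group | Power, t-test | Power, normal approximation |
|---|---|---|---|
| 0% | 26.0 | 78.5% | 80.1% |
| 5% | 24.7 | 76.3% | 78.0% |
| 10% | 23.4 | 74.0% | 75.8% |
| 15% | 22.1 | 71.4% | 73.4% |
| 20% | 20.8 | 68.7% | 70.8% |

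At 20% loss the chance of missing a true 7-point difference is 100 − 68.7 = 31.3%, against the planned 20%.

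**Step 4. Sensitivity to the SD.** Pooling the two pilot SDs with equal weight (the pilot group sizes are not given) yields √((7.6² + 9.6²)/2) = 8.66. T-test power at 26 per group is then 81.6%, and at 25 per group 80.0%. At 9.6, the larger pilot SD, power at 26 per group is 73.2%.

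**The case against.** The strongest reply is that nothing is miscalculated. That stands: 26 per group is what the standard formula gives, and the 1.5 points between it and the t-test result are a matter of convention. A reader might infer from the 78.5% that the sample size contains an arithmetic error. The figures do not support that.

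A second reply is that SD 9 is already cautious and that matching may help. This stands in part. At the pooled pilot SD, power with full follow-up is 81.6%. Matching could also raise the power of the planned unpaired test: simulated at SD 9 with 26 per group, it is about 80% at an assumed within-pair correlation of 0.1 and 81% at 0.2. So a reader who concludes that 80% is out of reach for this design goes too far, since that holds only at SD 9 with no gain from matching. But the plan claims neither margin as cover for loss. The pooled-SD margin is used up by one child lost per group, and the larger pilot SD points the other way.

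A third reply is that loss rates are invented and that an article may leave retention assumptions to the full protocol. The rates are indeed assumptions. The equality of the required and recruited numbers is not: both stand in the article.

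Finally, three camps per arm in "groups of 9 to 13 children" imply at least 3 × 9 = 27 children against 26 per arm. A reader might take this as further evidence about power, or as hidden recruitment above 52. It is neither. It is a one-child operational mismatch, to be reconciled separately.

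**Conclusion.** The concern holds in a limited form. The 26 per group is correct by the normal approximation and has no slack. Recruitment is fixed at exactly that number, so the stated 80% does not allow for any loss. It is also stated for 3 weeks and not for the 26-week primary outcome.

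At SD 9, the planned t-test has about 79% power with all 52 children assessed, about 74% with 10% loss and about 69% with 20% loss. These figures rest on two-sided testing, no gain from matching, assumed loss rates, and the same difference and SD at 26 weeks as at 3 weeks. The document supplies neither a loss rate nor 26-week values.

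The point concerns what the trial says about its power. The choice of test and the treatment estimate are unaffected.

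**What to change.** Keep 52 children and make these changes:

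1. Reconcile the 3-week time point in the Sample size section with the 26-week primary outcome, and say which comparison the calculation supports.
2. After the sample size, state the power of the planned test, for example: *With all 52 children assessed, power of the independent t-test is about 79% (80% by the normal approximation) for a 7-point difference with SD 9; assuming the same difference and SD at 26 weeks, it is about 74% with 10% loss and 69% with 20% loss.* Say that the loss rates are assumed, or replace them with a rate the investigators can justify.
3. Separately, reconcile 26 children per arm with three camps of at least 9.

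The cost is a sentence or two in the Sample size section and a minor correction on camp size. No extra children are needed, and the stated power becomes somewhat less favourable.
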